| STUDY ARMS / PRODUCT(S) | 
The study consists of 2 infant formula arms i.e.:
 
 
Test product: Partially hydrolysed 100 percent whey protein based infant formula containing scGOS/lcFOS.
 
Control product: Intact cow's milk protein based infant formula (whey:casein ratio of 60:40) containing scGOS/lcFOS.
 
 
In addition, a breastfeeding arm is added to be used as a reference arm.
                                                                                                                                                                                                                                                                                                                                                                                                                                                                                                                                                                                                                                                                                                                                                                                                                                                                                                                                                                                                                                                                                                                                                                                                                                                                                                                                                                                                                                                                                                                                                                                                                                                                                                                                                                                                                                                                                                                                                                                                                                        |

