| STUDY OBJECTIVES        | 
To investigate the effects of a partially hydrolysed whey protein based infant formula (pHP formula) in healthy term infants until 17 weeks of age on growth, blood parameters, safety, and gastro intestinal tolerance compared to standard infant formula.
 
Primary
 
The primary objective of this study is to investigate equivalence of weight gain per day from baseline until the age of 17 weeks in infants receiving partially hydrolysed proteins (test product) compared to infants receiving intact proteins (control product).
 
Secondary
 
The secondary objectives of this study are:
 
 
To investigate equivalence of weight gain per day in infants receiving formula containing partially hydrolysed proteins compared to infants receiving breast milk from baseline until the age of 17 weeks;
 
To investigate equivalence of other growth parameters (recumbent length, head circumference, mid upper arm circumference) in infants receiving formula containing partially hydrolysed proteins compared to infants receiving formula containing intact proteins or infants receiving breast milk from baseline until the age of 17 weeks;
 
To investigate equivalence of other growth z-scores parameters (weight-for-age, weight-for-length, length-for-age, BMI-for-age, head circumference-for-age, mid upper arm circumference) in infants receiving formula containing partially hydrolysed proteins compared to infants receiving formula containing intact proteins or infants receiving breast milk at the age of 17 weeks;
 
To investigate the effect on blood parameters in infants receiving formula containing partially hydrolysed proteins compared to infants receiving formula containing intact proteins or infants receiving breast milk at the age of 17 weeks;
 
To assess the effect on safety in infants receiving partially hydrolysed proteins compared to infants receiving formula containing intact proteins or infants receiving breast milk from baseline until the age of 17 weeks;
 
To assess the effect on gastrointestinal tolerance in infants receiving formula containing partially hydrolysed proteins compared to infants receiving formula containing intact proteins or infants receiving breast milk from baseline until the age of 17 weeks.
 
 |

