| STUDY DESIGN       | This is a randomised, controlled, double blind, parallel group, multi-country, Phase IIb study.                                                                                                                                                                                                                                                                                                                                                                                                                                                                                                                                                                                                                                                                                                                                                                                                                                                                                                                                                                                                                                                                                                                              |
| STUDY DIAGRAM      | 
The study diagram illustrates the flow of participants through three main study arms. It begins with 'Healthy Term infants' (n = 224) who are randomised into two formula arms: 'Test product: partially hydrolysed proteins' (n = 112) and 'Control product: intact proteins' (n = 112). A third arm, 'Full breastfeeding for at least 17 weeks' (n = 60 to 112), is also shown. The diagram tracks participants through 'Visit 1' (Screening and randomisation, age 0-14 days), 'Visit 2' (4 wk), 'Visit 3' (8 wk), 'Visit 4' (13 wk), 'Visit 5' (17 wk), and 'Call 1' (19 wk). It also indicates 'any feeding' status and 'any adverse events, concomitant medication or nutritional supplements and GI tolerability'. The number of evaluable infants (n*) is noted as 78 for each formula arm and 78 for the breastfeeding arm.
 
n* = number of evaluable infants
                                                                                                                                                                                                                                                                                                                                          |

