| SUBJECTS           | 
To complete this study with a total of 156 evaluable infants, approximately 224 healthy term infants will be enrolled in the two infant formula arms, anticipating a dropout rate of 30%. In addition, a maximum of 112 healthy term infants will enrol in the non-randomised breastfeeding reference arm. Recruitment for this breastfeeding reference arm stops when:
 
 
- Either at least 60 infants are enrolled in the breastfeeding reference arm while at the same time-point the infant formula arms are fully enrolled OR
 
- 112 infants are enrolled in the breastfeeding reference arm while at that time-point the infant formula arms are not fully enrolled yet and recruitment for these arms continues.
 
                                                                                                                                                                                                                                                                                                                                                                                                                                        |
| INCLUSION CRITERIA | 
 
1. Healthy term infants (gestational age <math>\geq 37</math> weeks + 0 days and <math>\leq 41</math> weeks + 6 days);
 
2. Infants' age at enrolment <math>\leq 14</math> days;
 
3. Birth weight within normal range for gestational age and sex (10th to 90th percentile according to the WHO Child Growth Standards – or local growth standards if available);
 
4. Head circumference at inclusion within normal range for age and sex (within 2 SD curves according to WHO Child Growth Standards – or local growth standards if available);
 
5. Infant formula arms: infants who are exclusively formula fed by time of randomisation with a maximum infants' age of 14 days (infants of mothers who choose not to breastfeed or mothers who cease breastfeeding for any reason before the infant is 14 days of age);
OR
Breastfeeding reference arm: infants who are exclusively breastfed and whose mothers are intending to exclusively breastfeed their infant at least until the infant is 17 weeks of age;
 
6. Written informed consent from parent(s) and/or legal guardian(s) aged <math>\geq 18</math> years.
 
 |

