| STATISTICAL ANALYSIS | 
The main statistical technique will be “repeated measurement” mixed models with randomised group as fixed factor. Sex and country are stratification factors used in the randomisation and therefore will be included in the models. Birth weight will be included as covariate in the primary model (i.e., the model on weight gain per day). The impact of factors that may influence the intervention effect may be evaluated by adding them as (time varying) covariates.
 
For concluding equivalence on the primary outcome parameter, the two-sided 90% confidence intervals for the differences in mean weight gain per day from baseline to 17 weeks of age will be calculated. Equivalence between the arms will be demonstrated at the 5% significance level, if the two-sided 90% confidence intervals for the differences in mean weight gain per day between the arms lies entirely between -3 g/day and +3 g/day. The margin of <math>\pm 3</math> g/day will be used if the pooled standard deviation (SD) of test and control group is equal or smaller than 6. If the pooled standard deviation is bigger than 6, an equivalence margin of <math>0.5 \times \text{SD}</math> will be used.
 
Equivalence in a secondary growth parameter is demonstrated at the 5% significance level if a two-sided 90% confidence interval for the difference in mean gain per day from baseline to 17 weeks of age between test and control lies entirely between <math>-0.5 \times \text{SD}</math> and <math>+0.5 \times \text{SD}</math>. SD is the pooled standard deviation of the gain per day (in growth parameter) from baseline anthropometric visit to 17 weeks of age computed from infants receiving test and control product.
 
Equivalence (at week 17) in a secondary z-score growth parameter is demonstrated at the 5% significance level if a two-sided 90% confidence interval for the difference in mean z-score between test and control lies entirely between -0.5 and +0.5.
 
The statistical analyses for the assessment of tolerance, safety parameters, blood parameters will be descriptive.
 |

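### Equivalence to breast milk is a secondary objective, but the analysis text is built for test versus control and commits to too little adjustment for a self-selected, non-randomised arm

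*Protocol*

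**What the plan says.** All references are to the protocol synopsis.

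- **Study objectives (secondary).** The first item asks for equivalence in weight gain, worded as "per day in infants receiving formula containing partially hydrolysed proteins compared to infants receiving breast milk from baseline until the age of 17 weeks". The next two ask for equivalence of the other growth gains and of the growth z-scores, against both control formula and breast milk. For blood parameters, safety and tolerance the objectives speak only of an effect.
- **Study arms / product(s) and Subjects.** The breastfeeding arm "is added to be used as a reference arm", and "a maximum of 112 healthy term infants will enrol in the non-randomised breastfeeding reference arm". Recruitment to it may stop once "Either at least 60 infants are enrolled in the breastfeeding reference arm while at the same time-point the infant formula arms are fully enrolled".
- **Inclusion criteria, item 5.** The formula arms take infants whose mothers chose not to breastfeed or stopped for any reason before 14 days of age. The breastfed arm takes infants whose mothers intend exclusive breastfeeding to at least 17 weeks.
- **Statistical analysis.** The main technique is "mixed models with randomised group as fixed factor". On covariates, the section says: "Sex and country are stratification factors used in the randomisation and therefore will be included in the models". Birth weight is added in the weight-gain model. Further factors may be added, but none is named. The weight-gain rule is ±3 g/day on a 90% interval. It refers to the arms and to intervals in the plural, but takes its SD condition from test and control. The rules for secondary gains (±0.5 SD) and z-scores (±0.5) name only test and control, and the SD for the gain margin comes from those two arms.
- **Other parameters.** Age at enrolment, gestational age, birth weight, mode of delivery, parental height, weight and BMI, education and maternal smoking in pregnancy are all collected.

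**The concern.** The objectives use equivalence for the growth outcomes and a weaker word for the others, so a formal conclusion against breast milk appears to be intended. Two things stand in its way.

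First, the analysis text was written for another contrast. A factor defined by randomised group has no level for an arm that was not randomised, and no equivalence rule names the breastfed arm.

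Second, the two sides of the contrast are formed by the mother's feeding choice and by whether breastfeeding was stopped early. Entry timing differs too: under Study description, formula infants enter once exclusively formula fed, and breastfed infants enter on consent and eligibility. The outcome is gain per day from baseline, so a systematic difference in baseline age would feed straight into it. Sex and country are in the model because they stratified the randomisation, which gives no protection for an arm outside the randomisation.

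An equivalence finding would be read as a statement about the formula. The interval would in fact cover feeding effect plus selection, and its nominal 5% error rate would apply to that sum. A false finding of equivalence and a false failure to show it are both possible.

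**Working it through.** **1. The plan's own figure.** The plan states "approximately 224 healthy term infants will be enrolled in the two infant formula arms, anticipating a dropout rate of 30" per cent, with 156 evaluable (78 per formula arm). 78 / (1 − 0.30) = 111.4, rounded up to 112 per arm; 2 × 112 = 224. This reproduces exactly, so the point is not one of arithmetic.

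**2. Objective against rule.**

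| Outcome versus breast milk | Equivalence an objective? | Does a rule cover it? | Committed covariates |
|---|---|---|---|
| Weight gain | Yes | Ambiguous: refers to the arms, but the SD condition uses test and control | Sex, country, birth weight |
| Other growth gains | Yes | No: test versus control, SD from those two arms | Sex, country |
| Z-scores at 17 weeks | Yes | No: test versus control | Sex, country |

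**3. What residual bias would do to the weight-gain rule, if it is extended to the breastfed arm.**

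Inputs:
- Margin m = 3 g/day and a 90% interval, critical value 1.645 (Statistical analysis).
- SD = 6 g/day. This is an assumption: 6 is only the threshold at which the margin switches to 0.5 × SD, and 0.5 × 6 = 3. No planning SD is given.
- n = 78 in each arm. The study diagram's evaluable number "is noted as 78 for each formula arm and 78 for the breastfeeding arm".
- Bias of 0.5 to 2 g/day: an assumed range.

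Formula, normal approximation, with d the apparent difference:
P(declare equivalence) = Φ((m − d)/SE − 1.645) + Φ((m + d)/SE − 1.645) − 1, with SE = 6 × √(1/78 + 1/78) = 0.961.

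True difference at the margin (3 g/day), bias towards zero b, so d = 3 − b:

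| b (g/day) | d | P(declare equivalence) |
|---|---|---|
| 0 | 3.0 | 5% |
| 0.5 | 2.5 | 13% |
| 1.0 | 2.0 | 27% |
| 1.5 | 1.5 | 47% |
| 2.0 | 1.0 | 66% |

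For b = 1: Φ(1/0.961 − 1.645) + Φ(5/0.961 − 1.645) − 1 = Φ(−0.604) + Φ(3.559) − 1 = 0.273.

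In the other direction, with no true difference and a bias of 1 g/day away from zero, the chance of showing equivalence falls from 86% (d = 0) to 66% (d = 1).

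**4. Size of the breastfed arm.** Recruitment may stop at 60, which cannot yield the 78 evaluable in the diagram. If the 30% loss also applies here (an assumption), 60 × 0.70 = 42. Then SE = 6 × √(1/78 + 1/42) = 1.148, and the chance of showing equivalence at zero difference is 67%, against 86% with 78. A bias of 1 g/day towards zero then gives 22% at the margin.

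**The case against.** Four points can be made for the plan, and each stands in part.

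- **Adjustment is not absent.** A reader might infer that the breastfed contrast would be wholly unadjusted. The text does not support that: sex and country are in the models, birth weight is in the weight-gain model, and further covariates are allowed. The entry criteria also restrict every arm alike on term birth, birth-weight percentile, head circumference, age and maternal conditions affecting intra-uterine growth. What remains is that the committed set was chosen for a randomised comparison and the rest is optional and unnamed.
- **A weight-gain rule may exist.** The plural intervals and the reference to the arms can be read to include the breastfed arm. So for weight gain the rule is ambiguous, not missing. For secondary gains and z-scores no such reading is available.
- **No conclusion is claimed.** A reader might infer that the plan asserts an unsupportable result. It states an aim to investigate and openly labels the arm a non-randomised reference.
- **The SAP is not at hand.** Covariate lists and reference-arm models often sit there, and their absence here is not the point. The point is that the objective, the randomised-group factor and the test-versus-control rules are all in this document and do not agree.

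It is also fair that the documents cite no evidence linking feeding choice to particular covariates, and none that a bias of any given size exists. They establish the selection itself, through inclusion item 5, but not its strength.

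**Conclusion.** The point holds as a mismatch between objective and analysis, together with adjustment that is inadequate for a non-randomised contrast. Followed as written, the plan either gives no rule for the breastfed comparison (secondary gains, z-scores) or invites a weight-gain verdict in which feeding effect and selection cannot be separated.

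The figures are illustrations and do not carry the point alone. With SD 6, margin 3 and 78 per arm, a bias of 1 g/day towards zero takes false equivalence at the margin from 5% to about 27%; the same bias away from zero takes the chance of showing true equivalence from 86% to 66%. The SD, the bias sizes and the 30% loss in the breastfed arm are assumptions. The figures do not show that this trial is biased, and the primary comparison of test with control is untouched. This should be corrected, at the weight due to a secondary objective.

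**What to change.** - Estimate test versus breastfed in a separate model with feeding group as the factor. Adjust for a pre-specified set of baseline variables already collected: age at enrolment, gestational age, birth weight, parental BMI and height, education, maternal smoking, mode of delivery, sex and country.
- Report the result as an adjusted reference estimate with a confidence interval.
- Reconcile Study objectives with Statistical analysis in one of two ways. Either word the breastfed comparisons as supportive or descriptive, or name the contrast, its margin and the source of its SD for each outcome and label any equivalence statement as non-randomised.
- Keep test versus control as the confirmatory comparison.

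The cost is a wording change and one extra model on data already being collected. The downside is a weaker statement about equivalence to breast milk. Adjustment reduces the selection problem but cannot make the contrast a randomised one, so the label matters even with the fuller model.

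### The breastfeeding arm is shown with 78 evaluable infants, a number that only its 112 maximum can deliver; the stop rule allows closure at 60 enrolled, which gives about 42 at the same loss

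*Protocol*

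**What the plan says.** The Study Diagram row of the Protocol Synopsis describes the breastfeeding arm's enrolment as a range: "A third arm, 'Full breastfeeding for at least 17 weeks' (n = 60 to 112), is also shown". On evaluable infants it gives one figure: "The number of evaluable infants (n*) is noted as 78 for each formula arm and 78 for the breastfeeding arm".

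The Subjects row sizes the formula arms at 156 evaluable infants in total and adds: "approximately 224 healthy term infants will be enrolled in the two infant formula arms, anticipating a dropout rate of 30" percent. For the breastfed infants it sets a cap, "a maximum of 112 healthy term infants will enrol in the non-randomised breastfeeding reference arm", and two ways for recruitment to end. One is reaching 112. The other is: "Either at least 60 infants are enrolled in the breastfeeding reference arm while at the same time-point the infant formula arms are fully enrolled". This row gives no evaluable number for the breastfeeding arm.

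Under Study Objectives, the first secondary objective is equivalence of daily weight gain "in infants receiving formula containing partially hydrolysed proteins compared to infants receiving breast milk from baseline until the age of 17 weeks". Equivalence with breastfed infants is also an objective for the other growth measures and the z-scores.

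The Statistical Analysis row sets the criterion: "Equivalence between the arms will be demonstrated at the 5% significance level, if the two-sided 90% confidence intervals" lie within ±3 g/day, with 0.5 × SD replacing 3 when the pooled SD of test and control exceeds 6. No power, planning SD or assumed true difference is stated for any comparison.

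**The concern.** A range of enrolment cannot produce a single evaluable number, and here the lower end of the range is smaller than the evaluable number itself. Either the 78 describes only the most favourable case, or the stop rule is looser than intended.

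This matters because an equivalence conclusion depends on the width of the confidence interval, and the smaller arm contributes most to that width. Anyone reading 78 in all three arms would expect the breastfed comparison to be as precise as the randomised one. The stop rule does not secure that. If the arm closed near its minimum and equivalence with breastfed infants was not shown, the smaller arm alone could be the reason, and the plan would not have warned of it.

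**Working it through.** **Inputs from the protocol.** Formula arms: 224 enrolled, 156 evaluable, 30% dropout. Breastfeeding arm: 60 to 112 enrolled, 78 evaluable. Criterion: two-sided 90% confidence interval within ±3 g/day, or ±0.5 × SD if the SD exceeds 6.

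**Assumptions, not in the protocol.** The 30% loss, stated for the formula arms, also applies to the breastfeeding arm. The weight-gain margin applies to the comparison with breastfed infants. The test arm delivers its planned 78. The analysis is unadjusted. The SD and true difference are varied below.

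**Step 1: reproduce the plan's figures.** 78 / (1 − 0.30) = 111.4, rounded up to 112 per formula arm and 224 in total. This agrees with the plan.

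**Step 2: apply the same arithmetic to the breastfeeding arm.**
- Maximum: 112 × 0.7 = 78.4, so 78. Conversely, 1 − 78/112 = 30.4% loss, so the diagram's figure implies about the same loss.
- Minimum: 60 × 0.7 = 42.
- Minimum with no loss at all: 60, still below 78.

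The inconsistency at the lower end therefore does not depend on the loss rate. Only the value 42 does.

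**Step 3: what it means for precision.** The standard error is SD × √(1/n₁ + 1/n₂). The square root is 0.1601 for 78 v 78 and 0.1914 for 78 v 42. The interval is 0.1914/0.1601 = 1.20 times as wide, whatever the SD. At SD 6 the half-width is 1.645 × 6 × 0.1601 = 1.58 g/day against 1.645 × 6 × 0.1914 = 1.89 g/day.

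**Step 4: what it means for power.** For two one-sided 5% tests, with margin m and true difference d, the normal approximation is

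Power = Φ((m − d)/se − 1.645) + Φ((m + d)/se − 1.645) − 1.

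With m = 3, d = 0 and SD 6:
- 78 v 78: se = 0.961; 3/0.961 − 1.645 = 1.478; power = 2 × 0.930 − 1 = 86.1%.
- 78 v 42: se = 1.148; 3/1.148 − 1.645 = 0.968; power = 2 × 0.833 − 1 = 66.7%.

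The t-based version, simulated with 1,000,000 draws, gives 86% and 66%. Further t-based results:

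| SD (margin) | True difference | 78 v 78 | 78 v 60 | 78 v 42 |
|---|---|---|---|---|
| 5 (3) | 0 | 96% | 93% | 86% |
| 5.5 (3) | 0 | 92% | 87% | 77% |
| 6 (3) | 0 | 86% | 79% | 66% |
| 6 (3) | 0.5 | 80% | 74% | 62% |
| 6 (3) | 1 | 66% | 60% | 50% |
| 7 (3.5) | 0 | 86% | 79% | 66% |

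The 78 v 60 column is the minimum enrolment with no loss. At zero difference the SD 6 and SD 7 rows agree because the margin scales with the SD above 6.

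**The case against.** The strongest objection is about the source. The 78 for the breastfeeding arm appears only in a machine-generated description of a figure, parts of which are garbled. The Subjects row, which is ordinary text, gives an evaluable total for the formula arms alone. The original figure may print a range, or a 78 meant only for the formula arms. This objection stands as a condition: the figure has to be checked first.

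Second, a reader might infer that the plan leaves the breastfed comparison with 66% instead of 86% power. The document does not support that. It states no power and no planning SD. Six is only the point at which the margin rule switches, and at zero difference it is the least favourable SD, since power rises below it and is constant above it. At SD 5 the 42-infant case still has about 86%. The planned model also adjusts for sex, country and birth weight, which the calculation ignores. The 30% loss is stated for the formula arms, and the secondary growth and z-score criteria are worded for test versus control.

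Third, a reader might take 42 as the expected result. Sixty is a floor that applies only if the formula arms are already full, and any enrolment from 60 to 112 is possible. The interim analysis can only increase the sample size, which would give this arm longer to recruit. Nor does the document give grounds for supposing a higher loss among breastfed infants.

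Finally, the 60 to 112 range is disclosed beside the 78, the arm is a non-randomised reference, and the comparison is secondary. All of this limits the consequence. None of it makes a single 78 compatible with a minimum of 60.

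**Conclusion.** The point holds as an inconsistency of size, provided the original figure does show a single 78. That number matches only the maximum enrolment of 112 at 30% loss. At the minimum of 60, the arm yields about 42 if the same loss is assumed, and cannot yield more than 60 under any loss.

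The consequence is confined to the secondary equivalence comparisons with breastfed infants and is conditional. At 42 instead of 78 the confidence interval is about 20% wider. Power falls by about 10 points at SD 5, 15 at SD 5.5 and 20 at SD 6, for a margin of 3 g/day, zero true difference, 78 evaluable in the test arm and no covariate adjustment. These are illustrations, not figures of the plan, and they do not show that the comparison is unfit for an equivalence conclusion. The primary test-versus-control comparison is unaffected.

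**What to change.** 1. Check the evaluable number for the breastfeeding arm in the original diagram.
2. If it is a single 78, restate it as about 42 to 78, matching the enrolment of 60 to 112, and say that the 30% loss is assumed for this arm too.
3. Give the precision or power of the secondary equivalence comparison with breastfed infants at the lower limit, with the SD, margin, true difference and loss on which it rests.

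The cost is wording: a stated figure becomes less favourable, and no extra infants are needed. If the sponsor does intend 78 as a commitment, it is the closing rule that has to be reconciled with it, since 78 evaluable needs 112 enrolled at 30% loss. The point made here does not require that.
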